### Conclusions

The power analysis suggests that the study will be able to detect an increase in enrolment by 5%, a 0.2 difference in test scores and an increase in farmers’ incomes by 25% between the school feeding interventions and the control group. The study will be able to detect changes in enrolment by 6%, differences in tests scores by 0.3 and changes in income by 40% between the regular school feeding and the HGSF+ components of the intervention see (Table 7).

**Table 7 T7:** Summary table of values used in the power calculations

	**Enrolment**	**Test scores**	**Agricultural income**
Alpha	0.05	0.05	0.05
N (observations)	55	25	10
J (schools)	2	2	2
K (clusters)	58	58	58
Intra Cluster Correlation	-	0.15	0.25
Between sites variability	-	0.20	0.40

While the sample size is well suited to the analysis of programme impact on attendance rates and test scores, it is clearly insufficient for the analysis of income effects of the HGSF+ intervention. However, we hope to overcome this problem in two ways: by increasing statistical power through restricted randomisation and by focussing on intermediate outcomes rather than on household income, a variable that has large variance and high within cluster correlation. First, in order to increase statistical power we will adopt ‘restricted randomisation’ [25]. We will use the baseline data collected at the village and school levels to remove the randomisation outcomes that would result in an unbalanced comparison of project and control communes. The randomisation of the HGSF+ component of the project within the 58 communes will be performed only within the restricted sample of balanced randomisation outcomes. Second, we will analyse intermediate indicators of household income such as input use (labour and other farm inputs, such as land, seeds and fertiliser) and farm capital use like animal traction, tools and simple machinery.

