### Test scores

Few studies have investigated the impact of school feeding on learning outcomes. Drèze *et al*. [32] reviewed the experimental evidence on the impact of school feeding on standardised test scores and found an average standardised effect size of 0.31 for math achievement tests, while no effect was found on reading tests. We adopt a 0.3 difference as the expected effect of the intervention on math test scores. Based on the Scrochet report, the recommended intra-cluster correlation coefficient for math and reading tests is 0.15. We also assume that only about half of the children interviewed will be able to take the test and we set the number of children tested per village at 25. Simulations of power as a function of minimum standardised detectable effect show that a standardised difference of 0.1 would be detected in 24% of cases, a difference of 0.2 would be detected in 68% of cases and a difference of 0.3 would be detected in 95% of cases. With power set at 80%, the minimum detectable difference is 0.23.

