### Income

No previous studies have investigated the impact of home-grown school feeding on farmers’ incomes and indeed this type of programme is entirely new. In addition, it is difficult to find programmes with effects similar to those of school feeding programmes. The Purchase for Progress programme by the World Food Programme, which similarly to the Malian school feeding programme purchases food for local producers, has modelled an increase in income by $50 dollars as a reasonable target for small African farmers. With a per capita GDP of $700 this corresponds to 7.5% of the average Malian income, though the income of small farmers is likely to be less than half the national average income. In addition, farm income is about 50% of total household income and the impact of a $50 increase on farm income is therefore much larger. We adopt 15% and 30% as minimum detectable effects of the programme on agricultural incomes of small farmers.

We adopt a conservative estimate of 10 farmers surveyed in each village, and based on data on agricultural incomes of Ghanaian farmers, we estimated the intra-class correlation coefficient (ϱ = 0.25) and the variance explained by site variability (B = 0.40). Note that given the high value of the standard deviation of income, similar in size to average income, the standardised difference and the percentage difference are almost equivalent. The probability of detecting an increase by 15% in agricultural income is 35% and the probability of detecting an impact of 30% is 88%. A power of 80% will be able to detect an income increase by 26%.

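### The power conclusion lists a 0.2 SD test-score difference against control as detectable, but the plan's own calculation gives 68% power at 0.2 and an 80%-power limit of 0.23

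*Protocol article*

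**What the plan says.** All passages are in Appendix 1 of the protocol article.

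- **Conclusions**, on the school feeding interventions against control: "The power analysis suggests that the study will be able to detect an increase in enrolment by 5%, a 0.2 difference in test scores". The sentence goes on to a 25% increase in farmers' incomes. It names no power level.
- **Test scores**, same comparison: power is 24% at a standardised difference of 0.1; "a difference of 0.2 would be detected in 68% of cases"; "a difference of 0.3 would be detected in 95% of cases". Then: "With power set at 80%, the minimum detectable difference is 0.23".
- **Test scores**, planning values: "We adopt a 0.3 difference as the expected effect of the intervention on math test scores"; "the recommended intra-cluster correlation coefficient for math and reading tests is 0.15"; "we set the number of children tested per village at 25".
- **Income**, same comparison: "A power of 80% will be able to detect an income increase by 26" per cent.
- **Comparing school feeding to HGSF+**: limits at 80% power are 6% for enrolment, 0.32 for test scores (79% power at 0.3) and 40% for income. The Conclusions give these as 6%, 0.3 and 40%.
- **Table 7**, test-score column: alpha 0.05, 25 observations, 2 schools, 58 communes, intra-cluster correlation 0.15, between-site variability 0.20.

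**The concern.** A minimum detectable difference is a threshold. Rounding it up is harmless, but rounding it down claims a capability that the calculation denies. Here the plan computed power at exactly the value that the Conclusions put forward, and the result was 12 points below the 80% used for every other limit in the appendix.

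Learning is among the primary outcomes in the Abstract, and the section on main hypotheses expects only a moderate effect on test scores, so a true effect below the 0.3 planning value is plausible. The Conclusions paragraph is the place a reader is most likely to look for what the trial can show. Someone who takes 0.2 from it would think an effect of that size adequately powered, although by the Test scores section it would be missed about one time in three.

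**Working it through.** **1. Which power level the Conclusions use.** Set beside the sections they summarise:

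| Comparison | Outcome | Limit at 80% power in its section | Conclusions |
|---|---|---|---|
| Feeding vs control | Enrolment | 5% | 5% |
| Feeding vs control | Test scores | 0.23 | 0.2 |
| Feeding vs control | Income | 26% | 25% |
| HGSF+ vs regular | Enrolment | 6% | 6% |
| HGSF+ vs regular | Test scores | 0.32 | 0.3 |
| HGSF+ vs regular | Income | 40% | 40% |

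Three figures match exactly and three are rounded down. The implied standard is 80% power throughout.

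**2. Is the Test scores section consistent with itself?** I used a noncentral t with K − 1 = 57 degrees of freedom and two-sided alpha 0.05 (the plan does not state sidedness). A limit of 0.23 at 80% power implies a standard error of 0.0807. That standard error gives:

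- at 0.1: 23% (stated 24%)
- at 0.2: 68% (stated 68%)
- at 0.3: 95.5% (stated 95%)

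So 68% and 0.23 belong together, and 0.2 is not a limit at 80% power.

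**3. From the inputs.** For a cluster trial blocked by commune,

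Var(effect) = [s² + 4(ρ(1 − B) + (1 − ρ)/n)/J]/K,

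with ρ = 0.15, n = 25, J = 2 and K = 58. B is the share of between-cluster variance removed by blocking. s² is the between-site variance of the effect, which the plan does not state; I varied it as an assumption.

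- B = 0, s² = 0: [2 × (0.15 + 0.034)]/58 = 0.006345, SE 0.0797. Power at 0.2 is 69%; limit 0.227.
- B = 0, s² = 0.01: SE 0.0807. Power 68%; limit 0.230.
- B = 0.20, s² = 0: [2 × (0.12 + 0.034)]/58 = 0.005310, SE 0.0729. Power 77%; limit 0.208.
- B = 0.20, s² = 0.05: SE 0.0786. Power 71%; limit 0.224.
- B = 0.20, s² = 0.07: SE 0.0807. Power 68%; limit 0.230.

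No two-sided variant reaches 80% at 0.2. With s² = 0, reaching it would take about 75 communes (B = 0) or 63 (B = 0.20), against 58 planned.

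**4. Size.** The stated miss rate at 0.2 is 100 − 68 = 32%, against the 20% that an 80%-power limit implies. Moving the limit from 0.23 to 0.20 would need a variance of (0.20/0.23)² = 0.76 of the present one, a cut of about 24%.

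**5. Income.** The stated 26% limit implies a standard error of 0.0912 and about 77% power at 25%. Table 7's inputs (ρ = 0.25, B = 0.40, n = 10) with s² = 0 give [2 × (0.15 + 0.075)]/58 = 0.007759, SE 0.0881, a limit of 25.1% and about 80% power at 25%. The income gap is one point, and the inputs do not settle which of the two figures is right.

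**The case against.** The strongest defence is that this is rounding in a summary. The test-score limits there carry one decimal, so 0.23 becomes 0.2 and 0.32 becomes 0.3; the exact limit and the 68% are printed earlier in the same appendix, and nothing is hidden. That is fair, and it makes this a wording correction. It does not clear the figure, because the rounding goes in the unsafe direction and costs 12 points of power.

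A second defence is that the Conclusions may follow Table 7 rather than the Test scores section, since B = 0.20 with no effect variance gives a limit of 0.208. That may explain where 0.2 comes from. Power at 0.2 is then still only 77%, and it contradicts the stated 68%. A one-sided 5% test with B = 0 would reach about 80%, but it contradicts the 68% too.

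Three stronger readings are tempting and are not supported:

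- A reader might infer that the trial is too small for test scores. It was planned on 0.3, with 95% stated power; the 0.2 is not the planning effect.
- A reader might infer that every summary figure is flattering. Both enrolment figures and the HGSF+ income figure match their sections exactly.
- A reader might infer that the income figure is wrong by more than a point. Back-fitting to the rounded powers of 35% and 88% gives 26.7%, which matches neither the stated 26% nor the 25.1% from Table 7.

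Nor do the documents say that a null result will be judged against this paragraph; the misreading described above is a risk, not something the plan prescribes.

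**Conclusion.** The point holds as an overstated summary figure. At the plan's own 80% standard the test-score limit against control is 0.23, not 0.2, and stated power at 0.2 is 68%. My recomputed range at 0.2 is 68% to 77%, for effect variance between 0 and 0.01 without credit for blocking, or 0 to 0.07 with Table 7's B = 0.20. It assumes a two-sided 5% test with 57 degrees of freedom. The contradiction between 0.2, 0.23 and 68% needs none of these assumptions, because all three figures are the plan's own. The consequence is confined to how the trial's sensitivity on a primary outcome is described. The income and HGSF+ test-score roundings are minor and matter only for consistency.

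**What to change.** In the Conclusions of Appendix 1, for school feeding against control, replace 0.2 with: 0.23 (68% power at 0.2). State that all the detectable differences listed are at 80% power. For consistency with their own sections, give the income limit against control as 26% instead of 25%, and the HGSF+ versus regular feeding test-score limit as 0.32 instead of 0.3. Do not put in a back-fitted income value such as 26.7%, which would create a new mismatch with the Income section.

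The cost is an edit to two sentences and slightly less favourable figures. The sample size, the randomisation and the analysis stay as they are.

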### Main hypotheses and outcome indicators

We summarise here the expected impact of the intervention on education, nutrition and social protection discussed in Section Programme theory of the intervention.

•The intervention will have an impact on a small number of farmers in the intervention villages. Other persons in the village may benefit either directly or indirectly via an increase in income.

•The intervention will have a positive impact on enrolment, attendance and drop-out rates.

•The intervention will have an impact on cognitive abilities and class behaviour, including attention.

•The impact on learning (test scores) will be moderate as school quality is unlikely to change in the short term.

•The intervention will have a limited impact on physical growth of children because of the increase in PAL, substitution effects and the age range (6 to 17 years) of the targeted population. An impact on siblings of school-going children is possible if substitution effects are strong.

•The intervention will have a moderate impact on the diet because food purchases by communities and mayors do not follow nutritional guidelines and nutrition education is absent.

•The intervention will have little or no impact on micronutrient status as the food provision is not fortified and only moderate effects on diet diversity are expected.

•The overall impact of the programme will increase through the introduction of social accountability mechanisms and the strengthening of the monitoring and communication system.

Table 2 includes a list of the main outcome indicators of the study. Section Methods of analysis will describe how data will be collected using different survey instruments. All outcomes, including school attendance and test scores, will be obtained at the household level.

**Table 2 T2:** Main outcome indicators of the intervention

** Indicator**	** Metric**
Income	Farm profits
Distributional effects	Small farmers participating in the programme
Schooling	Enrolment, attendance, and completion
Attention	Digit span or other test
Learning achievements	Scores on language and math tests
Physical growth	Anthropometric measures of height and weight
Diet diversity	Household consumption
Social accountability	Parental monitoring and motivation

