### Enrolment

Public education in Mali is compulsory for nine years from age 7 to age 15 and split in a six-year primary cycle and a three-year lower secondary cycle. Enrolment rates in rural areas are very low and lower for girls compared to boys. Table 6 below reports the attendance rates for the age groups 7 to 12 and 13 to 15 in rural Mali calculated from the DHS survey of 2006 (Table 6).

**Table 6 T6:** Attendance rates for the 7 to 12 and 13 to 15 age groups in rural Mali (calculated from DHS, 2006)

	**Primary (age group 7 to 12)**	**Lower secondary (age group 13 to 15)**	**Age group 7 to 15**
All	35.6	33.8	35.1
Male	39.1	39.9	39.3
Female	32.1	27.4	30.8

Ahmed [34] found a 14% difference in enrolment rates between project and control groups in Bangladesh. Researchers for FAO/WHO [21] found an effect of 6% in Burkina Faso, Jacoby [35] found a difference of 3% in Peru, while Buttenheim *et al*. [36] found no effect in Laos, mostly due to lack of intervention implementation. We adopt an increase in attendance rate by five percentage points as a minimum expected impact of the programme. Simulations of power for the percent difference in enrolment in the project group versus the control group show that a 5% difference will be detected with 80% probability, while differences of 10% and 15% will be detected with certainty. At 80% power, the minimum detectable difference is 5%.

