### Comparing school feeding to HGSF+ (cluster randomized trial)

To estimate MDES we assume that 58 clusters (schools) will be randomly assigned to regular school feeding or HGSF+. Using standard simulations we observe that

•A 5% difference will be detected with 60% probability, while differences of 10% and 15% will be detected with certainty. At 80% power the minimum detectable difference is 6%.

•A standardised difference of 0.1 would be detected in 15% of cases, a difference of 0.2 would be detected in 41% of cases and a difference of 0.3 would be detected in 79% of cases. With power set at 80% the minimum detectable difference is 0.32.

•The probability of detecting an increase by 15% in agricultural income is 17% and the probability of detecting an impact of 30% is 50%. A power of 80% will be able to detect an income increase by 40%.

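### The claim that the sample suits attendance and test scores holds for school feeding versus control; for HGSF+ versus regular feeding, only increments about as large as the planned feeding effect are detectable

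*Protocol article*

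**What the plan says.** Appendix 1 sets planning effects for school feeding against no feeding. Under Enrolment: "We adopt an increase in attendance rate by five percentage points as a minimum expected impact of the programme". Under Test scores: "We adopt a 0.3 difference as the expected effect of the intervention on math test scores". For that comparison the 80%-power detectable differences are given as 5% (enrolment) and 0.23 SD (test scores).

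For the second comparison, "we assume that 58 clusters (schools) will be randomly assigned to regular school feeding or HGSF"+. On enrolment, power at a 5% difference is given as 60%, and "At 80% power the minimum detectable difference is 6"%. On test scores, power is given as 15%, 41% and 79% at 0.1, 0.2 and 0.3 SD, with a detectable difference of 0.32 SD at 80% power.

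The Conclusions restate both sets of detectable differences, with 0.32 shown as 0.3. They then give the judgement: "While the sample size is well suited to the analysis of programme impact on attendance rates and test scores". The one exception is the income effect of HGSF+, and the two remedies that follow are offered for that income problem.

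The hypothesis that the second comparison serves is under Main hypotheses and outcome indicators: "The overall impact of the programme will increase through the introduction of social accountability mechanisms and the strengthening of the monitoring and communication system".

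**The concern.** HGSF+ is the regular programme plus a capacity-building package, so HGSF+ versus regular feeding measures an increment between two fed groups. The protocol gives no expected size for that increment. It gives detectable differences, and these are no smaller than the effects it plans for feeding against nothing. A sentence that exempts only income from its assurance therefore credits the second comparison with a capability on education that its figures do not show.

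School participation and learning are among the primary outcomes in the abstract, and the Cost effectiveness section singles out the social accountability component as of particular interest. If the package adds a moderate amount, a non-significant education result is the likely outcome, and the protocol as worded gives no warning of that.

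**Working it through.** **Inputs from the protocol**
- Table 7: "Alpha 0.05 0.05 0.05" (sidedness not stated; two-sided assumed).
- 58 clusters in the HGSF+ comparison, 29 per arm (Table 3).
- Test scores: "we set the number of children tested per village at 25"; intra-cluster correlation 0.15.
- Enrolment: 55 children per community, attendance 35.1% at ages 7 to 15 (Table 6), no intra-cluster correlation given (dash in Table 7).
- The 5% and 6% differences are read as percentage points, as the Enrolment section words the planning effect.

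**1. Reproducing the test-score figures, HGSF+ versus regular**

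SE = √[(4/58) × (0.15 + 0.85/25)] = √(0.06897 × 0.184) = 0.1126 SD. Power is from the noncentral t on 56 df, with the normal approximation as a check.

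| Difference (SD) | Stated power | t | Normal |
|---|---|---|---|
| 0.1 | 15% | 13.8% | 14.2% |
| 0.2 | 41% | 41.5% | 42.7% |
| 0.3 | 79% | 74.4% | 75.9% |

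The detectable difference at 80% power is 0.321 (t) or 2.8016 × 0.1126 = 0.316 (normal). The stated 0.32 reproduces; the stated 79% does not. The two also conflict directly: 80% power at 0.32 implies about 75% at 0.3, and 79% at 0.3 would imply a detectable difference of about 0.304.

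**2. Enrolment, HGSF+ versus regular**

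The 6 points cannot be derived without an intra-cluster correlation. With a two-proportion test deflated by the design effect 1 + 54 × ICC, and ICC as an assumption:

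| Assumed ICC | Power at 5 points | Detectable at 80% |
|---|---|---|
| 0 | 83% | 4.8 points |
| 0.010 | 65% | 6.0 points |
| 0.015 | 58% | 6.5 points |
| 0.05 | 33% | 9.3 points |

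The stated pair (60% and 6 points) therefore corresponds to an ICC of about 0.010 to 0.015. The rest takes the stated figures as given.

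**3. Detectable increment against planning effect**

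| Outcome | Planning effect, feeding vs none | Detectable, feeding vs control | Detectable, HGSF+ vs regular |
|---|---|---|---|
| Enrolment | 5 points (a minimum) | 5 points | 6 points |
| Test scores | 0.3 SD (math) | 0.23 SD | 0.32 SD |

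**4. Power for an increment of half the planning effect**
- Test scores, 0.15 SD with SE 0.1126: about 26%. For 80% power (normal approximation) the communes needed are 4 × 0.184 × (2.8016/0.15)² = 257, against 58.
- Enrolment, 2.5 points: 60% power at 5 points implies SE 2.22 and gives 20%; 80% at 6 points implies SE 2.10 and gives 21%.

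**The case against.** Five objections deserve an answer.

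- **The 5 points is a floor.** The Enrolment section cites effects from none to 14% and takes 5 points as the least it expects. This stands: 6 points exceeds the adopted planning value, not every effect the protocol thinks possible. For test scores the excess is only 0.02 SD.
- **HGSF+ may add a lot.** A reader might infer that HGSF+ would have to more than double the programme's effect to be detected. The documents do not support that, because it assumes that regular feeding already delivers the full planning effect. The protocol lists late, uncertain and mis-sized deliveries in the regular programme, says results depend critically on implementation, and expects that effectiveness could be considerably improved. If regular feeding achieved nothing and HGSF+ achieved 7 points (an illustration), power with SE 2.22 would be about 87%. But the protocol gives no size for the increment, and a full 5 points against nothing would still have only the stated 60%.
- **The sentence may mean feeding versus control only.** This is possible, and on that reading it is true. It fits poorly with a sentence that follows a summary of both comparisons and excepts only HGSF+ income.
- **The limits are disclosed.** The Conclusions do print 6%, 0.3 and 40%. The fault is in the judgement drawn from them, not in concealment.
- **Precision may be better than calculated.** Restricted randomisation and regression on baseline data could help every outcome. If 20 to 30% of the variance were explained (an assumption), 0.32 would fall to 0.32 × √0.8 = 0.29 or 0.32 × √0.7 = 0.27. That would remove the small excess over 0.3 SD but would not make half-sized increments detectable. The protocol does not quantify the gain.

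**Conclusion.** The point holds in a limited form. The adequacy statement is supported for school feeding versus control. For HGSF+ versus regular feeding, the sample can reliably detect only increments about as large as the planned feeding effect itself (6 points, 0.32 SD). Power is 60% at 5 points and 74 to 76% at 0.3 SD. At half the planning effect it is about 20% on enrolment and 26% on test scores.

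These results rest on a two-sided test, the stated inputs with no covariate gain, and, for enrolment, the protocol's own power figures, which depend on an unstated intra-cluster correlation. If that correlation is above about 0.015, the enrolment position is worse.

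Two further inferences are tempting but unsupported. One is that a null is bound to be reported as proof that the training adds nothing; the protocol does not say how it will read such a result. The other is that implementation measures should be ranked first for this comparison; no power calculation supports that either, and commune-level measures also rest on 58 units.

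**What to change.** In the Conclusions of Appendix 1:

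1. Limit the statement of suitability for attendance and test scores to school feeding versus control.
2. State that for HGSF+ versus regular feeding the sample can detect only increments about as large as the planned feeding effect on attendance and test scores, and is insufficient for smaller ones, as well as for income.
3. Give 0.32 rather than 0.3 SD for that comparison. In the section on that comparison, correct the 79% at 0.3 SD to agree with the stated inputs (74 to 76%).
4. State that HGSF+ education differences will be reported with confidence intervals, and that a non-significant result will not be taken as no added benefit. The reporting rule can be carried into the final analysis plan that the steering group is to approve.

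No new data, sample or analysis is needed. The cost is a few sentences, and a stated capability that looks less favourable.
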